***Recruitment***

Recruitment strategies will encompass both facility- and Veteran-based recruitment methods to maximize potential recruitment of OEF/OIF/OND Veterans. For facility-based recruitment, the research team may work with providers within the ECHCS to enlist their assistance with recruitment. Research team members may attend team meetings and/or brief staff about the study. Staff may pass along the approved flyer to Veterans who may be interested. Veterans may also see our approved flyer within the facility. In addition to recruiting from facilities within the ECHCS, the research team will recruit Veterans in the community who are eligible to receive VHA care. Approximately 60% of Veterans do not seek care within VHA [74]. Recruiting members of this population is expected to facilitate overall participant accrual, increase participation by women and minorities, and maximize the generalizability of findings. The Rocky Mountain MIRECC collaborates with partner organizations within the community to enhance representation of Veterans not seeking VHA care. In addition, the study will be advertised on the internet via MIRECC affiliated websites, and approved letters describing the study and inviting participation will be sent to those who have participated in past studies and have been added to the Rocky Mountain MIRECC research data repository.

Given that some Veterans may have limited contact with Veteran Affairs Medical Centers (VAMCs), and as a result be unlikely to learn about the opportunity to participate in the study through normal means (e.g., advertisements within the VA Medical Center, provider referral), we will also engage in Veteran-based recruitment strategies. Veterans will be identified in the Corporate Data Warehouse (CDW) for possible eligibility for this study. CDW is a national repository comprising data from several VHA clinical and administrative systems, organized into a collection of data domains. Individuals with ICD-9 and ICD-10 codes of interest (e.g., G47.00) will be identified from various tables within the CDW that correspond to diagnoses given at inpatient/outpatient VA visits and fee-basis visits. Similarly, other insomnia related variables within the electronic medical record or CDW (e.g., notes associated with sleep consults or treatment, medication and problem lists, service connection, mental health assistant assessments) may also be used to identify individuals for recruitment purposes. Demographic data within the CDW and the Veterans Business Administration (VBA) will also be used to determine eligibility. Names and addresses of Veterans who may be eligible will be pulled from the CDW and/or VBA for recruitment purposes. An initial invitation may be sent by U.S. mail from the study PI, to participate in the study with a pre-stamped and addressed ‘Refusal Response Card’. If the potential participant contacts the study team and expresses interest in participating, he/she may then be screened for possible enrollment into the study. The refusal response card will not include any PHI, nor the study name or Veteran’s name. So that the research staff is able to identify a Veteran who would no longer like to be contacted, the refusal response card will include a randomly-generated unique identifier number so that the research team can link the person’s response with their identity using the unique identifier. The refusal response card only states, “I do not wish to participate in this study.” If the potential participant returns the refusal response card, that individual’s name will be flagged as ‘do not contact.’ One additional letter inviting participation may be sent if the participant has not expressed either interest in participating, or no interest in participating by returning the refusal response card, within 4 weeks of the initial letter being sent out. Potential participants recruited after obtaining their name and address and relevant diagnoses from the CDW and/or VBA will be formally consented prior to any study activities taking place.

***Inclusion/Exclusion Criteria***

**Inclusion Criteria:**

1. Age between 18 and 55
2. History of deployment in the Global War on Terror
3. Eligible to receive care through VA ECHCS
4. Reliable access to the Internet
5. English speaking
6. Able to provide informed consent
7. Current insomnia diagnosis as defined by Diagnostic and Statistical Manual of Mental Disorders 5 (DSM 5) criteria [45]

**Exclusion Criteria:**

1. Currently enrolled in/participating in other intervention research studies
2. Other untreated sleep disorders (e.g., sleep apnea, periodic limb movement)
3. Currently receiving formal psychological treatment for insomnia (not including sleep medications)
4. Past 3 month change in schedule and/or dosage of medications that are designed to improve/impact sleep
5. History of Bipolar Disorder (with manic episodes), Schizophrenia, Schizoaffective Disorder, or a Psychotic Disorder
6. Untreated seizures or seizure disorder
7. Physical illness that is active, unstable, degenerative, and/or progressive
8. Currently pregnant or plan to become pregnant in the next 6 months
9. Irregular work schedule, shift work, and/or life changes (e.g., new baby) interfering with regular sleep patterns
10. Significant cognitive impairment, as determined by chart review and/or during screening, that would interfere with ability to engage in SHUTi
11. Current non-alcohol Substance Use Disorder, excluding Cannabis Use Disorder, as determined by chart review and/or self-report screen of drug use (> 1 time) in past 3 months
12. Current alcohol use diagnosis, as determined by SCID 5 module, in the past 3 months
13. **Study Design and Research Methods**

**Figure S1.** Consolidated Standards of Reporting Trials (CONSORT) diagram.

[figure not shown]

***Screening Examinations & Procedures***

A Veteran expressing interest in participating in this study will participate in a screening process to assess for study inclusionary/exclusionary criteria. A waiver of consent (including waiver of written documentation) and a HIPAA Waiver of Authorization will be requested (see screening script with verbal consent) for the screening portion of the study. This screening process, which will be conducted by a member of the research team, may include a review of medical records and/or a brief phone interview. During the screening, a screening form will be used to facilitate acquisition of basic information to assist in determination of the inclusion/exclusion criteria. The screening form will not contain PHI. However, personal information is required for participant contact and electronic medical record review for confirmation of medical/psychiatric history. Screening data will be kept separate from other study data. Once interest in the study has been conveyed and screening procedures have been completed, a member of the research team will explain the intervention/assessment procedures to the participant. If the participant is eligible and agrees to participation in the study, the research team member will continue on with the consent process. If necessary, another phone appointment may be scheduled to complete the consent process.

***Consent Procedures***

All study procedures will be conducted via the telephone and the Internet. For this reason, we are requesting a wavier of documentation of consent and HIPAA. A consent process will still occur over the telephone with all eligible participants.

**Assessing ability to provide consent**. Individuals interested in participating will be assessed for their ability to provide informed consent, based on their responses to the following questions:

1. What are you being asked to do if you participate in this study?
2. Finish this sentence – The purpose of this study is to find out…
3. True or False: After beginning this study, you can decide to not continue at any time, without penalty.
4. What should you do if you have questions about this study?
5. Who should you call if you feel you have been harmed in this study?
6. What are the risks of being in the study?
7. What are the benefits of being in the study?

If the individual is able to adequately answer these questions and decides to participate, verbal assent will be obtained. Individuals who are not able to adequately respond to the questions above will be excluded from participation. Participants will be provided with ample time to ask questions.

Following the consent process, including the consent questions, potential participants will be asked to verbally provide their assent. Participants will be able to view the postcard consent upon their initial login to the study website.

Enrollment into the study will be documented in the participant’s electronic VA medical chart.

***Assessment & Intervention Procedures***

Following the consent process, while on the telephone, the research team member will provide the participant with the web address for the B*e*Health Solutions Vets Sleep registration website. The participant will visit this website to register. Once registered, study staff will confirm the participant’s registration, which will then send an automated email to the participant inviting them to the B*e*Health Solutions Vets Sleep study-specific website. At this website, participants will have the ability to review the postcard consent and set up their user profile which will then allow the participant to establish their personal login and password.

The procedures above will ensure that participants are correctly accessing the web-based platform that has been specifically designed for the Vets Sleep research study (i.e., not accessing any B*e*Health Solutions/Pear Therapeutics SHUTi products that are meant for the public domain/commercial entity). As part of the grant funding supporting this research, Denver Research Institute (DRI), the non-profit organization managing the grant, has a contract with B*e*Health Solutions. As part of this contract, B*e*Health Solutions/Pear Therapeutics will provide 113 SHUTi licenses and 113 educational website control licenses.

*Sleep Diary Pre-Assessment:* After enrollment in the study, participants will then be provided instructions on how to complete a two-week sleep diary assessment online via the study website. Participants will be informed that they must complete 10/14 sleep diaries in order to move forward in the study. For each sleep diary (1/day), participants will be compensated $1, for a total of $14.

*Baseline Assessment:* After completing at minimum 10/14 days of sleep diaries, participants will then be invited to complete their baseline assessment (see Table S1 above). Participants will be compensated $50 for baseline assessment. Participants may receive a phone call or email reminding them to complete the baseline assessment.

*Random Allocation and Concealment:* Random allocation will be conducted by the Study Coordinator after baseline assessment completion; randomization will be stratified by suicide attempt history. The randomization scheme will be produced using Statistical Analysis System (SAS) PROC PLAN with a specified seed and random block sizes, prior to any recruitment and will be conducted by [name]. To ensure concealed allocation, participants will be designated by an identification (ID) number. ID numbers will only be forwarded to the Study Coordinator, who will randomly allocate participants based on the randomization scheme. In this way, only the Study Coordinator (not the participant, blind assessor, or other research personnel involved in data acquisition) will know condition assignment.

*Intervention:* Following the baseline assessment, up to 226 Veterans will be randomized to SHUTi (n = 113) or the educational website control (n = 113). These interventions will run for nine weeks.

*SHUTi*: SHUTi is a self-guided (i.e., automated), interactive, and tailored web-based program modeled on the primary tenants of face-to-face CBT-I. Intervention content is delivered through six “cores.” Users will obtain access to a new core based on a time and event-based schedule (e.g., seven days after completion of previous core); ISI is administrated in tandem with completion of each core. This schedule is consistent with the recommendation from a task force commissioned by the Academy of Sleep Medicine, which deemed that an average of six to eight sessions constitutes “adequate treatment exposure” [75]. The SHUTi program relies on user-entered online sleep diaries to track progress and to tailor treatment recommendations (i.e., assign a “sleep restriction” window). Each core acts as an online analog for the weekly sessions typically used when delivering CBT-I in a face-to-face format, following the same general structure: 1) core objectives (what will be learned and why this information is important); 2) review of previous week’s homework and sleep diary data; 3) new intervention material; 4) assignment of homework (treatment strategies for the coming week); and, 5) a summary of the core’s main points. Intervention content is enhanced through a variety of interactive features, including personalized goal-setting, graphical feedback based on inputted symptoms, animations/illustrations to enhance comprehension, quizzes to test user knowledge, patient vignettes, and video-based expert explanation. Automated emails are sent to encourage program adherence which is an important component to facilitate adherence and outcomes in self-guided Internet delivered interventions, especially for patients with comorbid or elevated symptoms [29].

*Educational Website Control:* The educational website control used in this RCT has been previously developed by University of Virginia researchers. When developing the educational website control, researchers conducted a thorough online review to determine what constituted “treatment as usual” for patient education websites targeting insomnia. Informed by this review, the educational website control was designed and includes the following: 1) content presented all at once; 2) treatment information about insomnia symptoms, diagnosis and differential diagnosis of insomnia, etiology, the natural history of insomnia and its prognosis, and cognitive-behavioral treatment strategies; 3) printable documents (including sleep diaries and insomnia severity assessments); 4) a FAQ section which provides answers to frequently encountered patient problems; and, 5) automated email prompts to encourage users to return to the site. Non-automated individual patient inquiry elements, such as forums and “ask the expert,” are not included as these can confound the obtained content (as different users may or may not receive helpful content, if anything at all). As indicated above, a detailed FAQ section is included, which parallels this type of content but in a more systematic way.

*Post-Intervention Assessment:* Following the intervention period, all allocated participants will be contacted to complete the post-intervention assessment. Participants will receive a phone call or email reminding them to complete the post-intervention assessment online via the web-based platform. The study team member coordinating the assessment will be blind to the participant’s group membership. To ensure that both the blind assessor and study participant do not gain information relevant to their group assignment, the blind assessor will remind the participant at the beginning of the reminder call to not discuss information about their web-based participation as this information may signal whether the participant received SHUTi or the educational website control. After each post-intervention assessment reminder, the blind assessor will be asked to record whether the participant broke the blind. Please see Table S1 for a list of all post-intervention assessments. Participants will be compensated $50 for the post-intervention assessment.

*Sleep Diary Post-Intervention Assessment*. After completion of the post-intervention assessment, participants will be asked to again complete two weeks of sleep diaries using a web-based interface. For each sleep diary (1/day), participants will be compensated $1, for a total of $14.

*Six-month and One-year Post-Intervention Follow-up Assessments.* All allocated participants will be contacted to complete follow-up assessments using the procedure outlined in the post-intervention assessment. Please see Table S1 for a list of all follow-up assessments. Participants will be compensated $40 at each follow up. Participants may receive a phone call or email reminding them to complete the follow-up assessment. Participants will receive a reminder card about their upcoming follow-up assessment at roughly three and nine months since enrollment.

**D. Description, Risks and Justification of Procedures and Data Collection Tools:**

All participants will be provided with ample time to ask questions prior to enrolling in the study. As noted above, a series of questions will assess participants’ understanding of the study in order to ensure that participants have adequately comprehended the critical information (e.g., risks/benefits, voluntary nature) and are able to provide informed consent. Participants will be clearly informed that the study is voluntary and that they can withdraw from the study at any time, with no penalty. Additionally, all research staff have been trained in human subjects research.

**Adverse Events**

Significant adverse events are not expected. For the purpose of this study, adverse events are defined as symptoms reported by participants that are directly related to participating in the study. The PI will be responsible for monitoring adverse events and will regularly review data for safety monitoring to ensure adherence to the protocol and standard operating procedures regarding participant safety. All adverse events will be reported to COMIRB within five days of learning of such events. Due to the limited risks of participating in this study, an external Data Safety Monitoring Board will not be appointed. Furthermore, any participants who reports adverse events may be contacted by [name] to discuss resources and care that the VA can provide.

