**Risks**

The anticipated risks and discomfort associated with research procedures are not greater than those that would be ordinarily encountered during routine clinical care or psychological assessment. Additionally, many Veterans who participate in research of this nature report positive experiences. However, there is potential risk that the subject matter of the study assessments may cause participants to feel uncomfortable or upset. Consequently, the voluntary nature of the survey will be emphasized during recruitment and informed consent. Additionally, although we are not targeting a high-risk population for recruitment in this study (i.e., there is no inclusion criteria regarding suicidal ideation/attempt), resources (e.g., Veterans Crisis Line; information on how to access emergency care; the PI’s phone number) will be provided to all Veterans in the consent form and online platform, in case participants wish to speak to someone about their participation in the research study or about VA resources; these safeguards will help to mitigate this potential risk.

Participants randomized to SHUTi may experience increased tiredness due to restricted time in bed (this is part of the behavioral treatment for insomnia). To minimize the risk associated with sleep restriction, the SHUTi platform does not recommend participants restrict sleep fewer than five hours. The initial assigned sleep window is also comparable to how much total sleep the participant gets (based on individualized sleep diary data), but the sleep time is restricted to a smaller window. For example, rather than allowing a participant to get 6 hours of sleep while spending 8 hours in bed, a participant will be asked to spend only 6 hours in bed. To further minimize risks associated with sleep restriction, we will instruct participants that they may contact us if they have significant concerns. Based on the situation, we will provide recommendations, including changing their sleep window or incorporating naps. Participants will also be told to avoid operating a car or other heavy machinery when they feel tired. As needed, we will instruct participants to contact their primary care provider or seek professional help at a sleep clinic.

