**Safety Monitoring**

Based on the topic of this study, it is not believed that participating in the study places participants at increased risk. However, some participants may be at risk for suicidal ideation due to factors beyond the study and participants will be asked about several suicide risk factors during assessments. There are no clinical cutoffs for the Adult Suicidal Ideation Questionnaire that indicate definite or imminent risk for suicide and no total score is associated with an indication for immediate treatment. During the consent process, all participants will be informed that study team members will not be actively monitoring assessment responses and that immediate clinical needs should be addressed by calling the Veteran’s Crisis Line or 911. The Veterans Crisis Line contact information will be embedded in the web-based platforms as a resource for Veterans who may need additional support, regardless of their score on any specific assessment. From a scientific perspective, it is also important to not provide active outreach/resources to some participants (based on potential total scores) as this could influence the nature of the intervention being provided and could interfere with our ability to determine whether or not the interventions delivered (SHUTi or Educational Website Control) were associated with decreases in suicide risk (Exploratory Objective 1.4). Notably, there is no evidence to suggest that asking about suicidal ideation increases risk for suicide.

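### The adverse-event definition makes relatedness a condition of counting and no instrument asks both arms about events, so adverse-event counts by arm will be incomplete and open to differential attribution

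*Protocol*

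**What the plan says.** The Adverse Events section of the Protocol states that "adverse events are defined as symptoms reported by participants that are directly related to participating in the study". Three conditions must hold together: the event is a symptom, the participant reports it, and it is directly related to participation. The section does not say who decides relatedness. The same definition governs IRB reporting: "All adverse events will be reported to COMIRB within five days of learning of such events". The investigator "will regularly review data for safety monitoring", without saying which data, and "an external Data Safety Monitoring Board will not be appointed".

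The Risks section names one expected effect, for one arm: "Participants randomized to SHUTi may experience increased tiredness due to restricted time in bed". To limit that risk, "we will instruct participants that they may contact us if they have significant concerns". Under Safety Monitoring, participants are told that "study team members will not be actively monitoring assessment responses".

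Table S1 lists the instruments at each time point. None is described as asking about adverse events, accidents or hospital admissions. Contact itself is the same in both arms: "All allocated participants will be contacted to complete follow-up assessments using the procedure outlined in the post-intervention assessment".

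**The concern.** Whether an intervention caused an event is best judged by comparing randomised arms on all events. If only events already thought to be related are counted, that judgement is made before the comparison, one participant at a time, by an unnamed judge. An accident or a hospital admission is not a symptom, so it falls outside the definition even if it followed from sleep restriction.

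Two errors are then possible. Complaints may be attributed more readily in the arm that was told to expect tiredness, which gives a false excess in SHUTi. Or attribution may be low in both arms, which hides a real excess and makes a report of no events look more reassuring than it is. An analysis plan written later cannot recover events that were not captured. The efficacy comparison is not affected.

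**Working it through.** The document states no adverse-event rate and no safety sample size, so there is no figure to reproduce. The check has two parts.

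**1. What is captured, and in whom**

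| Source | Arms | When | Free of attribution? |
|---|---|---|---|
| Adverse events as defined | Both, if the participant reports | Any time | No |
| ISI, Veteran's SF-36, ASIQ, PCL-5, BDI-II, BAI, MSRC Common Data Elements | Both | Times 1 to 4 | Yes |
| Life Experiences Survey; sleep and demographics follow-up questions | Both | Times 3 and 4 | Yes |
| Revised NEII and two Internet questionnaires | SHUTi only | Time 2 | No: they ask about the program |
| Reasons for Termination | SHUTi non-completers | Time 2, or at withdrawal | No |
| SHUTi follow-up questions | SHUTi only | Times 3 and 4 | No |

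The Life Experiences Survey looks back to the previous assessment. For anyone who completed Time 2, its Time 3 version starts after the nine-week intervention, so it misses the period in which sleep restriction is introduced. The last three rows, with the sleep-restriction instruction under Risks, are extra openings for SHUTi participants to link a complaint to the study. Under Post-Intervention Assessment, the blinded assessor also asks participants on reminder calls not to talk about their web-based participation. That protects the blind, but it discourages mention of the only problems that would count.

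**2. What differential or low attribution could do**

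Input from the Protocol (Intervention): n = 113 per arm. Assumed, and not in the document: true event rate p and attribution probability a. The recorded rate is r = p × a, and expected recorded events are 113 × r. The chance of a nominally significant difference (two-sided 0.05) is

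Φ[(|r1 − r2| − 1.96·SE0) / SE1], with SE0 = √[2·r̄(1 − r̄)/113] and SE1 = √[(r1(1 − r1) + r2(1 − r2))/113].

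Worked case: p = 20% in both arms, a = 80% in SHUTi and 20% in control.
- r1 = 0.16, r2 = 0.04, r̄ = 0.10.
- Recorded events: 113 × 0.16 = 18.1 and 113 × 0.04 = 4.5, from 22.6 true events per arm.
- SE0 = 0.0399, SE1 = 0.0391.
- (0.12 − 1.96 × 0.0399)/0.0391 = 1.07, and Φ(1.07) = 0.86.

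The range, with no true difference between arms:

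| True rate, both arms | Recorded at 80% vs 20% | Chance of false difference | Recorded at 50% vs 25% | Chance of false difference |
|---|---|---|---|---|
| 5% | 4.5 vs 1.1 | 30% | 2.8 vs 1.4 | 10% |
| 10% | 9.0 vs 2.3 | 54% | 5.7 vs 2.8 | 17% |
| 20% | 18.1 vs 4.5 | 86% | 11.3 vs 5.7 | 30% |
| 30% | 27.1 vs 6.8 | 97% | 16.95 vs 8.5 | 43% |

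The normal approximation runs high when counts are small. Summing the binomial probabilities of all count pairs with Fisher's exact p ≤ 0.05 gives 13.0%, 44.2%, 82.5% and 96.5% for the 80%/20% column. The pattern is the same.

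With equal attribution in both arms there is no false difference, but a real one is diluted. For true rates of 20% vs 10%, the same formula gives power of 56% with full capture, and 43%, 30% and 17% at 75%, 50% and 25% attribution.

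A report of zero events is weakened in the same way. The usual 95% upper bound is 3/113 = 2.7%, but it applies to the recorded rate. The bound on the true rate is 2.65%/a: 5.3% at a = 50% and 10.6% at a = 25%.

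**The case against.** The strongest reply is that the trial does collect a good deal of harm-relevant information without any attribution. Seven instruments go to both arms at all four time points, and the analysis plan for Exploratory Objective 1.4 compares ASIQ, BAI, BDI-II and PCL-5 between groups. Worsening suicidal ideation is therefore compared by arm. This stands. A reader might infer from the definition that unattributed events are never recorded, or that the arms' safety cannot be compared; the document supports neither. Nor can it be shown that accidents or self-harm are absent from the data, because the items of the Common Data Elements and the Life Experiences Survey are not reproduced.

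Controls are not without a prompt. Before enrolment every participant must adequately answer a question on whom to call if harmed, and all receive the investigator's phone number. This also stands: the imbalance is one of degree. Nor does the text say that the participant must make the attribution; it leaves unstated who decides relatedness.

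The lack of active monitoring of responses does not mean data are missing. It limits timeliness, not collection, and the investigator's review is a stated safeguard of unstated content.

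Finally, fuller capture would still leave little power for uncommon events. At assumed rates of 3% vs 6%, Fisher's exact test with 113 per arm has about 11% power; at 3% vs 9%, about 38%. That limits what the fix can deliver, but it does not justify counts that may be biased. The scales measure average symptom change; they do not count discrete events.

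**Conclusion.** The point holds in a limited form. As written, the plan yields adverse-event counts that are incomplete and open to differential attribution, with no named judge of relatedness. This applies to tiredness, accidents and hospital admissions, for which Table S1 names no dedicated item. It does not extend to insomnia, mood, anxiety, PTSD symptoms, suicidal ideation or quality of life, which stay comparable between arms.

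The size is not known. The illustrations rest on assumed event rates of 5% to 30% and assumed attribution probabilities. Over these, the approximate chance of a false difference runs from 10% to 97%, and a real difference loses up to about two thirds of its power (56% to 17%). They show the direction and possible scale of error and predict nothing about this trial.

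The change should be made, because the lost information cannot be recovered afterwards and the change is cheap. It does not threaten the primary efficacy result. The absence of a planned adverse-event analysis is not part of the point, since that may sit in an analysis plan that is not shown.

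**What to change.** 1. In Adverse Events, define an adverse event as any untoward medical or psychological occurrence after randomisation, whatever its cause. Record seriousness and relatedness as separate fields, and name the role that judges relatedness.
2. Add one identical question on such events, including accidents and hospital admissions, to the Time 2, 3 and 4 online batteries in both arms. Mark each event as solicited or spontaneous, so that the extra SHUTi-only openings can be separated out.
3. Reword the IRB sentence so that the five-day report still applies to events judged related to participation. Without this, the wider definition would send every unrelated illness, over more than a year, into five-day reporting.
4. Since responses are not actively monitored, state when the solicited answers are reviewed and from what point the team is taken to have learned of an event.

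Cost: an amendment, a few more minutes per participant across three existing assessments, and more events to log and classify, which takes some staff time. No visits are added and no treatment changes. The question reaches only those who respond. With the planned minimum of 85 per arm at Time 2, zero events would give an upper bound of 3/85 = 3.5%, and only large differences in uncommon events could be detected.
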